# A pilot multicenter randomized controlled trial comparing Bankart repair and remplissage with the Latarjet procedure in patients with subcritical bone loss (STABLE): study protocol

**DOI:** 10.1186/s40814-022-00987-4

**Published:** 2022-01-31

**Keywords:** Shoulder, Instability, Randomized, Trial, Surgery

## Abstract

**Introduction:**

Anterior dislocations, the most common type of shoulder dislocation, are often complicated by subsequent instability. With recurrent dislocations there often is attrition of the labrum and progressive loss of the anterior bony contour of the glenoid. Treatment options for this pathology involve either soft tissue repair or bony augmentation procedure. The optimal management remains unknown and current clinical practice is highly varied.

**Methods and analysis:**

The Shoulder instability Trial comparing Arthroscopic stabilization Benefits compared with Latarjet procedure Evaluation (STABLE) is an ongoing multi-centre, pilot randomized controlled trial of 82 patients who have been diagnosed with recurrent anterior shoulder instability and subcritical glenoid bone loss. Patients are randomized to either soft tissue repair (Bankart + Remplissage) or bony augmentation (Latarjet procedure). The primary outcome for this pilot is to assess trial feasibility and secondary outcomes include recurrent instability as well as functional outcomes up to two years post-operatively.

**Conclusions:**

This trial will help to identify the optimal treatment for patients with recurrent shoulder instability with a focus on determining which treatment option results in reduced risk of recurrent dislocation and improved patient outcomes. Findings from this trial will guide clinical practice and improve care for patients with shoulder instability.

**Trial registration:**

This study has been registered on http://www.ClinicalTrials.gov with the following identifier: ClinicalTrials.gov Identifier: NCT03585491, registered 13 July 2018, https://www.clinicaltrials.gov/ct2/show/NCT03585491?term=NCT03585491&draw=2&rank=1.

**Ethics and dissemination:**

This study has ethics approval from the McMaster University/Hamilton Health Sciences Research Ethics Board (REB) (approval #4942). Successful completion will significantly impact the global management of patients with recurrent instability. This trial will develop a network of collaboration for future high-quality trials in shoulder instability.

**Supplementary Information:**

The online version contains supplementary material available at 10.1186/s40814-022-00987-4.

## Introduction

The shoulder is the most commonly dislocated joint in the body with a global incidence that ranges from 15.3 to 24.8 per 100,000 people [1–3]. In North America, a sampling of individuals presenting with shoulder dislocations to United States (US) emergency departments identified an overall incidence rate in the US of 23.9 (95% confidence interval, 20.8 to 27.0) per 100,000 person-years and a maximum incidence rate (47.8 [95% confidence interval, 41.0 to 54.5]) occurring in those between the ages of 20 and 29 years [1].

Anterior dislocations, the most common type of shoulder dislocation, are often complicated by subsequent instability, and recurrent dislocation, with reported rates as high as 42%. The affected population is primarily young males [2–4]. Shoulder instability commonly results in pain and negatively impacts quality of life [5]. Shoulder pathology is the third most common cause of musculoskeletal pain, and in the USA, estimated direct costs for the treatment of shoulder pathology account for over $7 billion USD annually [6]. A number of long-term studies have demonstrated an association between the recurrent instability episodes and the risk of degenerative arthritis and over 50% of patients with shoulder instability will go on to require surgical intervention [7–9].

With recurrent dislocations, there may be attrition of the labrum and progressive loss of the anterior bony contour of the glenoid in addition to the capsulolabral detachment [3, 10, 11]. Shoulders with recurrent instability that do not undergo operative management demonstrate a higher incidence of arthropathy in comparison to those which underwent surgical stabilization [9]. In instances where bone loss is not present, the capsulolabral soft tissue is repaired anatomically via open or arthroscopic means, referred to as a Bankart procedure. With increasing recognition of combined posterosuperior humeral head impaction, known as a Hill-Sachs lesion, this procedure has been increasingly coupled with tethering or tenodesis of the infraspinatus tendon into the Hill-Sachs lesion, known as a “remplissage” procedure [12–14]. Instances of significant bone loss (> 25%) are commonly treated with a non-anatomic reconstruction involving a bone transfer known as a “Latarjet” coracoid transfer procedure [15].

However, there is controversy regarding the optimal treatment of patients with a mild degree of bone loss (10–20%) [16]. Mild glenoid bone loss combined with humeral head defects is very common with reported rates ranging from 49 to 86% in cases of recurrent instability. It is often unrecognized and underestimated resulting in patients potentially being inadequately treated [17–20].

The more common arthroscopic capsulolabral procedures have strong advocates who argue that with modern techniques, arthroscopic management has acceptably low recurrence rates and restores the anatomy of the shoulder joint. Surgeons who prefer the Latarjet procedure cite the unacceptably high failure rates with soft-tissue stabilization [21]. Although retrospective clinical studies have suggested a reduced recurrence rate with the Latarjet procedure, there is a higher reported complication rate and potential morbidity associated with the open procedure [22, 23].

No comparative randomized control trial has been completed evaluating Bankart repair with concomitant remplissage in comparison to a Latarjet procedure in the setting of mild to moderate bone loss. Meta-analysis of available observational studies comparing arthroscopic Bankart repair and open Latarjet procedures suggests an increased risk of recurrent instability with Bankart repair (21.1%) in comparison to Latarjet (11.6%), Risk ratio (RR) = 1.97 (95% Confidence Interval (CI) 1.32–2.95) Additionally, an increased risk of re-dislocation was identified with 9.5% in those undergoing Bankart repair in comparison to Latarjet (5.0%), RR 1.87 (95% CI 1.04–3.34). Despite this, no significant differences in revision surgery rates for instability or rates of complications between patients treated with either procedure were identified [24]. A prospective trial is needed to identify the optimal treatment for patients with recurrent dislocations. A pilot study is needed prior to a large trial to determine the feasibility of a larger trial in terms of ability to recruit across clinical sites, adherence to study protocol, and ability to follow participants for 24 months.

## Objectives

Prior to a large trial, we will conduct a pilot trial comparing arthroscopic capsuloligamentous repair vs. coracoid transfer (Latarjet procedure) evaluating recurrent dislocation rates and functional outcomes over a 24-month period. The feasibility objectives are to evaluate (1) our ability to recruit patients across clinical sites, (2) our adherence to the study protocol, and (3) our ability to follow patients to 24 months.

Clinical objectives for the pilot trial are exploratory only. These will be the objectives of the definitive trial. We will compare arthroscopic capsuloligamentous repair (Bankart repair + Remplissage) vs. coracoid transfer (Latarjet procedure) on recurrent shoulder dislocations and symptoms of instability up to 24 months post-surgery; shoulder function; health-related quality of life; physical examination: range of motion, strength, stability, return to previous level of activity; and shoulder-related complications and serious adverse events.

## Methods

This trial was prospectively registered with clinicaltrials.gov before the first participant was enrolled (NCT03585491). This protocol is reported according to Standard Protocol Items: Recommendations for Interventional Trials (SPIRIT) reporting guidelines and the pilot results paper will follow the pilot study extension to the Consolidated Standards of Reporting Trials (CONSORT) guidelines.

### Design overview

We propose a multi-centre pilot parallel-group randomized controlled trial of 82 patients across Canada, the USA, and Europe to compare the effect of capsuloligamentous repair (Bankart procedure+ Remplissage) and coracoid transfer (Latarjet procedure) in patients with post-traumatic recurrent anterior dislocation. We will follow eligible and consenting participants for 24 months. We will assess clinical outcomes at 2 weeks, 3 months, 6 months, 12 months, and 24 months post-surgery (Figure 1).

**Figure 1 Fig1:**
[figure not shown]
Trial design overview

### Study setting

This pilot trial will be conducted at a number of clinical sites in Canada, the USA, and Europe. This study will be coordinated at McMaster University by the Centre for Evidence-Based Orthopaedics (CEO) who will be responsible for trial oversight, clinical site management, data management, data analysis, and knowledge dissemination.

### Eligibility criteria

Patients who meet the eligibility criteria outlined below are to be included in the STABLE study.

The inclusion criteria are:Men and women ages 18–50 years.Diagnosis of post-traumatic recurrent anterior dislocation. This will require a minimum of two episodes of shoulder dislocations with confirming physical examination eliciting unwanted glenohumeral translation with reproduction of symptoms.Mild glenoid bone loss as defined on computed tomography (CT) by standardized and reproducible best-fit circle technique. The circle will be drawn using an on-face 3D reconstruction of the glenoid approximating a normal glenoid. Patients will be included if the missing anterior glenoid is greater than 10% but is less than 20%.Provision of informed consent.

The exclusion criteria are:Patients with concomitant injuries (cuff tear).Previous shoulder surgery.Patients that will likely have problems, in the judgment of the investigators, with maintaining follow-up.Epilepsy.Patients who are or at risk of being incarcerated.Diagnosis of multidirectional instability.Cases involving litigation or workplace insurance claims [e.g. Workplace Safety and Insurance Board (WSIB)].Confirmed connective tissue disorder (Ehlers-Danlos, Marfans) or Beighton hypermobility score > 6.Pregnancy.

### Recruitment strategy and patient screening

Participating centres will identify patients with recurrent dislocation through outpatient clinics. The surgeon, designated fellow, or resident will conduct a history and physical examination. Patients who are potentially eligible based on history and examination will be invited to participate in the trial. If they agree, written informed consent will be obtained in accordance with Good Clinical Practice and local ethics procedures.

### Trial interventions

Participants will be randomly assigned to undergo arthroscopic capsuloligamentous repair (Bankart repair + Remplissage) or open or arthroscopic coracoid transfer (Latarjet procedure).

### Soft tissue stabilization (control)

For arthroscopic soft tissue repair, the participant will be placed in the lateral decubitus or beach chair position. Standard diagnostic arthroscopy will be performed. The anterior capsulolabral complex will be freed from the anterior aspect of the scapular neck. The anterior aspect of the scapular neck will be decorticated. A capsuloligamentous repair will be performed with the capsule shifted from inferior to superior and repaired on the glenoid face. The number of anchors used for the repair will be left to the discretion of the surgeon. The infraspinatus will be tenodesed into the Hill Sachs defect. Patients will be given a sling for 4 weeks, and participation in sports will not be allowed for 6 months.

### Arthroscopic or open Latarjet procedure (intervention)

The Latarjet procedure will be performed through either open or arthroscopic means left up to the discretion of the operating surgeon. With an open procedure, a deltopectoral approach will be performed, the coracoid will be osteotomized at its base, and the posterior surface flattened. The subscapularis muscle will be split longitudinally with a vertical capsule incision close to the glenoid rim. The coracoid will be positioned flush or slightly medial to the glenoid face and secured in a method up to the discretion of the surgeon. Patients will wear a sling for 4 weeks and undergo an identical standardized rehabilitation protocol to those in the control group. In patients who undergo arthroscopic Latarjet procedure, the procedure will be performed via minimally invasive arthroscopic portals.

### Co-interventions

All participants will follow a standardized 6-phase rehabilitation protocol following surgical intervention (Appendix A). All other peri-operative and post-operative interventions will be left to the discretion of the treating surgeon per local standard care.

### Minimizing expertise bias

Differential expertise bias will be limited by ensuring that all participating surgeons are fellowship trained in shoulder surgery and have performed a sufficient number of cases to limit the potential for expertise bias. Based on the available literature, a minimum of 50 cases of arthroscopic Bankart repair would be required for surgeons to meet our participation requirements [25]. Our participation requirement for surgeons performing open or arthroscopic Latarjet procedures would be experience with at least 20 cases as suggested by the literature to maintain the required proficiency [26–29].

### Randomization

To ensure concealed allocation, eligible patients will be randomized using a centralized online randomization system within the Research Electronic Data Capture (REDCap) system. We will use an allocation ratio of 1:1. We will use random block sizes of 4 and 6, and we will stratify by clinical site. A data manager generated the randomization sequence and is the only team member with access to the sequence. Site research personnel will randomize patients.

### Blinding

The study team including the treating surgeon and study coordinator cannot be blinded as they will be performing the procedure and/or will have access to post-operative imaging and clinical notes. Participants will not be blinded to procedure type given the incision with open coracoid transfer and arthroscopic capsuloligamentous repair are distinctive. However, the data analyst will be blinded to the treatment group. For the definitive trial, if one treatment group shows superiority, the trial steering committee will write two interpretation documents before they know which treatment is superior, one for superiority of Latarjet and one for superiority of Bankart repair. This will minimize interpretation bias [30].

## Outcomes

### Primary outcome: Feasibility

The primary outcome of the pilot study will be feasibility. Specifically, this will include (1) *Recruitment* (recruitment of 82 participants); (2) *Protocol adherence* (number of crossovers); and (3) *Follow-up* (proportion of participants followed at two years). The success of the pilot study will be based upon the following a priori thresholds: (1) Establish an average recruitment rate of 0.5 patients per month at each of 10 active sites, (2) 3 or fewer crossovers across the 82 enrolled patients, and (3) 70 of 82 participants (85%) achieving complete follow-up at 2 years.

### Secondary outcomes: Clinical outcomes

The secondary outcomes are exploratory for this pilot trial. The secondary (clinical) outcomes are:

#### Recurrent dislocation and symptomatic instability

This outcome is critically patient important and is objectively documented in the case of shoulder dislocation or in the case of recurrent symptomatic instability will be patient reported at follow-up.

#### Shoulder function

Measured by Western Ontario Shoulder Instability (WOSI) Index, American Shoulder and Elbow Society (ASES) score, and Shoulder Activity Scale. The WOSI is a self-administered quality of life outcome measure designed for clinical trials evaluating treatments for patients with shoulder instability. It has been shown to have high reliability, validity, and responsiveness [31]. The WOSI score is commonly utilized and has been shown to provide excellent ability to detect variability in severity of post-operative instability symptoms including following shoulder stabilization procedures [32]. The ASES score is designed to assess shoulder function including instability [33]. It allows for patient self-evaluation through 11 items that can be used to generate a score, divided into 2 areas: pain (1 item) and function (10 items).

#### Health-related quality of life

Measured using the EuroQol-5 Dimensions (EQ-5D).

#### Physical examination

Physical examination following surgery will be performed by the operating surgeon and will consist of functional assessment important to patients. Range of motion and strength as well as assessment of shoulder stability are commonly reported outcome measures in the literature when assessing success following shoulder instability surgery [5, 24]. Range of motion will be assessed in forward flexion, abduction, external rotation, and internal rotation. Stability will be assessed primarily via the apprehension-relocation physical examination maneuver which has demonstrated the highest sensitivity in the literature for the diagnosis of anterior instability [34].

#### Return to previous level of activity and sport

The majority of shoulder instability affects young individuals involved in athletic activities and sport. An important aspect in the success of surgical intervention is to return patients back to previous and desired level of activity [35]. This outcome will be patient-reported.

#### Shoulder-related complications and serious adverse events

Major complications will include symptomatic non-union of transferred bone block, hardware penetration into the joint, neurological or vascular injury, or deep vein thrombosis. Adverse events will be classified as serious or non-serious. All serious adverse events will be reported to the Methods Centre.

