### Data collection and participant follow-up

The number of patients approached, who are potentially eligible, who agree to participate, and who decline participation (with their reason for refusal) will be recorded. Once participants have provided informed consent, baseline demographics, relevant medical history, and details regarding their diagnosis will be collected from the participant, the attending surgeon, their medical record, and through physical examination. Participants will also complete the patient-reported outcome measures (PROMs) at the time of enrolment. After surgery, surgical and peri-operative details will be collected from the attending surgeon and the participant’s medical records. Adverse events occurring during the surgical procedure or perioperative period will also be documented. Post-operative radiographs will be ordered as standard of care. We will use a centralized REDCap system for all sites.

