### Follow-up visits

Participants will be followed for 24 months post-surgery. Efficacy and safety outcomes will be assessed at 2 weeks, 3, 6, 12, and 24 months post-surgery at regularly scheduled clinic visits. At each time point, participants will complete the PROMs. Physical examination will be performed at 2 weeks, 3, 6, 12, and 24 months post-surgery follow-ups. Shoulder-related adverse events and serious adverse events will also be documented. In cases where the participant does not return to the clinic, study personnel will contact the participant by telephone, text, email, or standard mail. A missed follow-up form should be completed if the participant misses the follow-up visit. The schedule of events (Table 1) details the requirements and procedures for each visit.

**Table 1 Tab1:** Schedule of events

Assessment/procedures	Visit 1: Enrollment/screening	Visit 2: Surgery	Visit 3: 2 weeks post-surgery (± 7 days)	Visit 4: 3 months post-surgery (± 14 days)	Visit 5: 6 months post-surgery (± 30 days)	Visit 6: 12 months post-surgery (± 30 days)	Visit 7 24 months post-surgery (± 60 days)
Eligibility screening	●						
Informed consent	●						
Collection of demographic, medical history, radiograph	●						
Collection of surgical data		●					
Surgery		●					
WOSI	●		●	●	●	●	●
ASES	●		●	●	●	●	●
Shoulder Activity Scale	●		●	●	●	●	●
EQ-5D	●		●	●	●	●	●
Patient Satisfaction Scale	●		●	●	●	●	●
Physical examination	●		●	●	●	●	●
Radiograph (standard of care, **Latarjet only**)			●				
Follow-up form			●	●	●	●	●
Safety assessment		●	●	●	●	●	●

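### The only scheduled post-operative radiograph is for Latarjet patients, so hardware penetration, which can occur in both arms, is looked for on film in one arm only

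*Protocol article*

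**What the plan says.** The Protocol article, under Shoulder-related complications and serious adverse events, defines the listed events: "Major complications will include symptomatic non-union of transferred bone block, hardware penetration into the joint, neurological or vascular injury, or deep vein thrombosis". Non-union is qualified by symptoms and tied to the bone block. Hardware penetration carries neither a symptom condition nor an arm.

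Both procedures leave hardware in the shoulder. For the control repair, "The number of anchors used for the repair will be left to the discretion of the surgeon"; for Latarjet, the coracoid is "secured in a method up to the discretion of the surgeon".

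On imaging, the text and the schedule differ. Data collection and participant follow-up states: "Post-operative radiographs will be ordered as standard of care", with no arm and no time point. Table 1, under Follow-up visits, has one post-operative row, "Radiograph (standard of care, Latarjet only", with a single mark in the column "Visit 3: 2 weeks post-surgery (± 7 days". The other radiograph in the table is the enrolment item, "Collection of demographic, medical history, radiograph", which is pre-operative and applies to everyone.

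The Objectives section includes "shoulder-related complications and serious adverse events" among the outcomes on which the arms are compared. The Secondary analysis section plans descriptive summaries, with proportions or risk measures where appropriate and 95% confidence intervals, and no p values.

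**The concern.** A between-arm comparison of an event needs the event to be looked for in the same way in both arms. Here a listed major complication that is possible in both arms has a scheduled film in one arm and none in the other. Because the definition asks for no symptoms, an incidental film finding qualifies as an event. A silent penetration would then be recorded after Latarjet and missed after soft tissue repair, and the difference would look like a difference in safety.

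What is at stake is the Latarjet-versus-control estimate for this one item. The Objectives section says that the pilot's clinical objectives will be those of the definitive trial, so an uneven definition and schedule could carry over unless corrected now.

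**Working it through.** **Step 1: who can be counted, and how.** Safety assessment is scheduled in both arms at surgery and at 2 weeks and 3, 6, 12 and 24 months. The radiograph is scheduled in one arm, at 14 ± 7 days, that is days 7 to 21. Following Table 1 as written:

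| Hardware penetration | Latarjet | Soft tissue repair |
|---|---|---|
| Symptomatic | can surface at any safety visit | can surface at any safety visit |
| Silent | can be found on the 2-week film | no scheduled film |

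Equal visits make the first row even but not the second. The enrolment radiograph does not help, because it precedes the surgery.

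**Step 2: size.** The plan states no rate and no detection share for hardware penetration, so there is no figure to reproduce. Inputs:
- n = 82/2 = 41 per arm (Sample size section).
- t = true penetration rate, assumed equal in both arms; 2%, 5% and 10% are illustrations.
- Latarjet detection is assumed complete; the control arm is assumed to detect a share s.

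The recorded risks are t after Latarjet and s × t in controls. Hence:
- apparent risk ratio = t/(s × t) = 1/s, whatever t is;
- spurious risk difference = t × (1 − s);
- expected recorded cases = 41 × t after Latarjet and 41 × t × s in controls.

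| s | Apparent risk ratio | Difference, t = 2% | t = 5% | t = 10% |
|---|---|---|---|---|
| 1.00 | 1.00 | 0 points | 0 points | 0 points |
| 0.75 | 1.33 | 0.5 | 1.25 | 2.5 |
| 0.50 | 2.0 | 1.0 | 2.5 | 5.0 |
| 0.25 | 4.0 | 1.5 | 3.75 | 7.5 |

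Expected Latarjet cases are 41 × 0.02 = 0.8, 41 × 0.05 = 2.1 and 41 × 0.10 = 4.1. At s = 0.5 the control arm would record half of each: 0.4, 1.0 and 2.1.

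**Step 3: scale.** One event in either arm is 1/41 = 2.4 percentage points. This shows how coarse the estimate is; it does not measure the bias. With so few expected events the interval would be wide, but the shift in Step 2 is systematic and more patients would not remove it.

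**The case against.** The other side has several good points.

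- **The film is labelled standard of care.** The row records usual practice, and the text does not confine post-operative films to one arm, so some controls may be imaged. A reader might infer that no control patient is ever imaged; that holds for Table 1 only. This stands, and it is why s is unknown rather than zero. It also shows that text and table need reconciling.
- **Bias is possible, not shown.** The documents do not say that anchors are visible on plain film, or that penetration is equally likely with anchors and with bone-block fixation. Both points stand. They limit any claim about size, but if anchors were hard to see, detection would be no more even.
- **Non-union.** A reader might infer that a 2-week film is too early to show the listed non-union, which would then be under-recorded. The documents do not support this. The event is symptomatic non-union, which can come to light at the 3- to 24-month visits; it is confined to the Latarjet arm; and no time to union is given.
- **The other complications.** A reader might infer that the complication comparison as a whole cannot be interpreted. Neurological or vascular injury and deep vein thrombosis do not depend on this film, and no composite total is specified.
- **Importance.** A reader might take complications to be the main argument against Latarjet. The Introduction reports a higher complication rate but also cites a meta-analysis with no significant difference, and does not rank the arguments.
- **Status.** The primary outcome is feasibility and the clinical outcomes are exploratory. This stands and lowers the severity, though a descriptive risk ratio is distorted by unequal detection just as a tested one is.

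**Conclusion.** The point holds for hardware penetration only. As scheduled, a film-only penetration can be counted after Latarjet but is not looked for after soft tissue repair, and the likely direction is more recorded events after Latarjet. The size cannot be derived from the documents. The illustrative risk ratios of 1.33 at s = 0.75 and 2.0 at s = 0.5 rest on three assumptions: equal true rates, complete detection after Latarjet, and incomplete detection in controls. If detection were equal in practice, the distortion would vanish.

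Separately, the data-collection text and Table 1 do not agree on which arm is imaged and when, whatever view is taken of the bias.

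Severity is low. The outcome is secondary, exploratory and descriptive, and no sample size, error rate or feasibility threshold changes.

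**What to change.** No imaging need be added.

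1. For the between-arm comparison, count hardware penetration in both arms only when it is symptomatic or leads to reoperation.
2. Report penetration found solely on the 2-week Latarjet film on a separate line, so that no safety information is lost. If a reoperation was prompted by that film alone, mark it as such, because the film could otherwise re-enter the comparison by that route.
3. Reconcile the radiograph sentence under Data collection and participant follow-up with the Table 1 row, on arm and on time.
4. Record on the case report form any standard-of-care post-operative shoulder image taken in either arm, so that readers can see how much imaging each arm had.

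The cost is some definition wording and one case report form item on images already taken. The small downside is that asymptomatic film findings move from the comparative line to a separate one.
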